## Abstract

**Objective:**

To investigate whether continuous positive airway pressure during spontaneous breathing trial is non-inferior to pressure support by comparing both techniques in mechanically ventilated children.

**Methods:**

This is a multicenter, open-label, non-inferiority randomized controlled trial. The primary outcome is successful liberation from invasive mechanical ventilation for at least 48 hours post-extubation. Secondary outcomes include the need for post-extubation respiratory support and the length of stay in the pediatric intensive care unit. The sample size is estimated to be 170 participants. Non-inferiority will be assessed using the Farrington-Manning test. The trial registration number is NCT06593288 (clinicaltrials.gov). Infants older than 36 weeks corrected gestational age and < 18 years old admitted to the pediatric intensive care unit requiring invasive mechanical ventilation for at least 24 hours and ready to wean will be included. Patients with chronic pulmonary conditions, congenital heart disease, upper airway abnormalities, morbid obesity, and in palliative care will be excluded. Patients who have passed the extubation readiness test will be randomized to receive either continuous positive airway pressure or pressure support during a spontaneous breathing trial.

**Results:**

the results of the study should be ready and published within a year.

**Conclusion:**

The transition from mechanical ventilation to spontaneous breathing is a pivotal moment in the care of critically ill children. Yet, limited high-quality evidence informs the optimal approach to spontaneous breathing trials. Our protocol outlines a rigorously designed non-inferiority randomized controlled trial comparing spontaneous breathing trials conducted with and without pressure support.

## INTRODUCTION

While life-saving, invasive mechanical ventilation (MV) is associated with both short- and long-term complications.^(1)^ Once the underlying condition improves, timely weaning from ventilatory support is essential. Weaning is complex, often guided by unit protocols and physician experience rather than standardized techniques. Successful extubation is a key objective, and determining extubation readiness has become a significant focus of clinical research.^(2–4)2^

Although spontaneous breathing trials (SBTs) and extubation readiness tests (ERTs) are frequently used interchangeably, they differ in scope. Spontaneous breathing trials assess the ability to breathe spontaneously with minimal support. At the same time, ERT also evaluates additional factors such as sedation levels, neurological status, and the risk of upper airway obstruction.^(3,5)^ Spontaneous breathing trials have been associated with reduced MV duration, fewer complications, and lower healthcare costs in adults.^(6–10)^ In pediatric populations, daily SBTs have been shown to reduce the duration of MV by up to 30%.^(11)^

A survey of pediatric intensivists revealed that 86% use SBTs before extubation, with 50% following a protocolized approach.^(3)^ Despite its widespread use, the optimal technique and duration of SBT in children remain unclear. Standard methods for pediatric SBT include T-piece, continuous positive airway pressure (CPAP), or CPAP with low-level pressure support (PS).^(5,12)^

The use of PS during SBT is widely debated. Some argue that PS mitigates the resistance imposed by the endotracheal tube, while others claim this is a theoretical benefit without clinical backing. Studies suggest that PS may underestimate the post-extubation work of breathing, potentially leading to a higher rate of false-positive extubation readiness. Despite these concerns, PS remains the preferred method for many pediatric intensivists, supported by adult studies showing its efficacy in predicting extubation success.^(13,14)^

However, robust pediatric data comparing PS with other SBT methods is limited, and recent pediatric ventilator liberation guidelines have only conditionally recommended either PS or CPAP for SBT, citing low-certainty evidence.^(4)^ This trial will investigate whether CPAP during SBT is non-inferior to PS by comparing both techniques in mechanically ventilated children.

### Study design

This multicenter, open-label, non-inferiority randomized controlled trial will compare SBTs with PS and CPAP in mechanically ventilated children. The study "Protocol for a non-inferiority randomized controlled trial of sbt in children with and without pressure support" was approved by the Institutional Review Board of *Hospital das Clínicas* of *Faculdade de Medicina de Ribeirão Preto* (CAAE 82637424.6.1001.5440) on November 12^th^, 2024. Informed consent will be required for all participants. The trial will be conducted in two pediatric intensive care units (ICUs): the coordinating center is an academic center, *Hospital das Clínicas* of *Faculdade de Medicina de Ribeirão Preto*, *Universidade de São Paulo*, which has an 8-bed pediatric ICU, and *Instituto de Oncologia Pediátrica* (IOP - GRAACC), which has a 19-bed pediatric ICU and is an oncologic center. The Brazilian Research Network in Pediatric Intensive Care (Brnet-PIC) supports the study.

Recruitment will begin in June 2025 and is expected to be completed by June 2026. The trial will follow the CONsolidated Standards Of Reporting Trials (CONSORT) guidelines, and the procedures will follow the ethical standards of the local committee on human experimentation and the Helsinki Declaration of 1975. The trial registration number is NCT06593288 (clinicaltrials.gov).

Figure 1 shows the schematic design of the study.

**Figure 1 f1:**
[figure not shown]
Schematic design of the trial.

### Eligibility criteria

#### Inclusion criteria

–Infants older than 1 month (> 36 weeks corrected gestational age) and children < 18 years old–Admitted to the participating pediatric ICUs requiring invasive MV for more than 24 hours–Clinically ready for weaning

#### Exclusion criteria

–Age < 1 month or > 18 years-old–Chronic pulmonary conditions, congenital heart disease, or upper airway abnormalities–Morbid obesity–Palliative care patients–Parental/guardian refusal

### Interventions

After passing the ERT, which is shown in table 1, patients will be randomized to either the PS or CPAP group. After consent, the local researcher will conduct randomization in REDCap electronic data capture tools hosted at the University of São Paulo. Both groups will undergo a 1-hour SBT. The PS group will receive PS adjusted according to the tracheal tube size, while the CPAP group will receive CPAP. The patient will be monitored during the SBT according to the worksheet in table 2.

**Table 1 t1:** Extubation readiness test worksheet

[figure not shown]

**Table 2 t2:** Monitoring the patient during the spontaneous breathing test

Extubation readiness test		
Desaturation SpO_2_ < 92% in patients without congenital heart disease or patients with acyanotic heart defects SpO_2_ decreased by > 5% from baseline in patients with cyanotic congenital heart disease	□ Yes	□ No
RR increased above the normal range	□ Yes	□ No
Exhaled VT < 4mL/kg	□ Yes	□ No
Respiratory distress indicated by accessory muscle use, diaphoresis, and nasal flaring	□ Yes	□ No
Hemodynamic compromise HR ± 20% from baseline BP ± 20% from baseline	□ Yes	□ No
Patient went into apnea with ventilator backup ventilation	□ Yes	□ No
ETCO_2_ > 55mmHg or increase by 10mmHg or by 20% from baseline	□ Yes	□ No

If all the above checks in table 2 are NO at the end of a 1-hour spontaneous breathing test, inform the pediatric intensive care unit team of patient readiness for extubation, set a time for extubation, and decide on the post-extubation respiratory support level. If, for some reason, the patient is not extubated, justify:

SpO_2_ - peripheral oxygen saturation; RR - respiratory rate; VT - tidal volume; HR - heart rate; BP - blood pressure; ETCO_2_ - end-tidal carbon dioxide.

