### SBT Groups

–**CPAP Group:** SBT for 1 hour with positive end-expiratory pressure (PEEP) and no PS. The PEEP and FiO_2_ will remain the same as during the ERT.–**PS Group:** SBT for 1 hour with PEEP and PS, adjusted by tracheal tube size: PS = 6cmH_2_O for tubes > 5mm, 8cmH_2_O for tubes 4 - 5mm, and 10cmH_2_O for tubes ≤ 3.5mm.

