### Sample size and power calculation

Based on a previous study by Ferguson et al.,^(15)^ we estimate that 94 patients per group (188 total) will be needed to detect non-inferiority with 90% power and a 10% non-inferiority margin. Considering a 20% attrition rate, we plan to recruit 170 participants.

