### Statistical methods

The primary analysis will be performed according to the intention-to-treat principle. Non-inferiority will be assessed using the Farrington-Manning test, with a 90% confidence interval to confirm the non-inferiority of CPAP compared to PS.

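### The primary analysis is one overall Farrington-Manning test across two unlike ICUs; a centre-stratified risk difference would guard against chance centre imbalance at essentially no cost

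*Protocol article*

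**What the plan says.** The Study design section names two sites. The coordinating academic centre is described as one "which has an 8-bed pediatric ICU"; the second site is one "which has a 19-bed pediatric ICU and is an oncologic center".

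Under Interventions, the allocation step is described in one sentence: "After consent, the local researcher will conduct randomization in REDCap electronic data capture tools hosted at the University of São Paulo". It gives the person, the time and the platform. It does not give the type of sequence, the block size or any strata, and it does not rule any of them out.

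Under Statistical methods, "The primary analysis will be performed according to the intention-to-treat principle", and "Non-inferiority will be assessed using the Farrington-Manning test, with a 90% confidence interval to confirm the non-inferiority of CPAP compared to PS". As named, this compares two overall proportions and has no term for centre. The margin comes from the Sample size section: "94 patients per group (188 total) will be needed to detect non-inferiority with 90% power and a 10% non-inferiority margin". The same section plans to recruit 170.

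**The concern.** Centre is a plausible predictor of reintubation. One unit treats oncology patients and the other is a general academic unit. The note under Table 2 also leaves the time of extubation and the level of support afterwards to the unit's own team. Those local decisions fall between randomisation and the 48-hour outcome, in an open-label trial.

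If success rates differ by centre, an arm that by chance holds more children from the better centre looks better for a reason unrelated to the breathing-trial method. A non-inferiority claim rests on whether a confidence limit clears a 10-point margin, so a shift of 1 to 3 points can decide a borderline result. An observed imbalance would also be visible to every reader of the report, and an overall test chosen in advance gives the authors no prespecified way to deal with it.

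**Working it through.** **1. The plan's own figure.** No success rate or alpha is stated, so 94 per group can be matched only by choosing them. With equal true rates p, margin 0.10, one-sided alpha 0.05 (what a two-sided 90% interval implies) and 90% power:

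n per group = (1.645 + 1.282)² × 2p(1 − p) / 0.10².

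p = 0.94 gives 97 and p = 0.95 gives 82; 94 needs p of about 0.942. The figure is neither confirmed nor refuted. The checks below use the planned 170 children, 85 per arm.

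**2. How large a centre imbalance can be.** Assume allocation without centre strata and 85 children per centre. The difference between arms in the share from one centre has SD about √(0.25 × 2/85) = 0.077. By simulation it is 10 points or more in about 19% of trials, and its 95th percentile is about 15 points. With a 30/70 split between centres the 95th percentile is about 14 points.

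**3. Shift in the estimate.** Shift = imbalance × difference in success rate between centres.
- Centres 10 points apart (95% and 85%, assumed): 0.153 × 0.10 = 0.015.
- Centres 20 points apart (97% and 77%, assumed): 0.153 × 0.20 = 0.031.

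That is about 1.5 or 3 points against a margin of 10.

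**4. Error averaged over all allocations.** In 200,000 simulated trials per scenario, with sizes of 188, 170 and 136 and centre differences of 0 to 20 points, one-sided type I error of the plain test without strata was 0.048 to 0.051 against a nominal 0.05.

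**5. Error given the imbalance that occurred.** Take a 15-point imbalance, centre rates of 95% and 85%, and CPAP truly 10 points worse in each centre (85% and 75%).
- Overall rates are 0.90 and 0.80. The plain test's standard error is √[(0.09 + 0.16)/85] = 0.0542, so the estimate must exceed the margin by 1.645 × 0.0542 = 0.0892.
- Within-centre variances average (0.0475 + 0.1275)/2 = 0.0875 for PS and (0.1275 + 0.1875)/2 = 0.1575 for CPAP. The standard error given the imbalance is √(0.245/85) = 0.0537.
- Imbalance favouring CPAP: P[Z > (0.0892 − 0.015)/0.0537] = P(Z > 1.38) ≈ 0.08.
- Imbalance favouring PS: P[Z > (0.0892 + 0.015)/0.0537] = P(Z > 1.94) ≈ 0.03.

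Simulation of the Farrington-Manning test itself gives, at 170 children:

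| Centre success (assumed) | Imbalance | Plain test, favours CPAP / PS | Centre-stratified test |
|---|---|---|---|
| 95% / 85% | 15 points | 0.081 / 0.025 | not run |
| 97% / 77% | 15 points | 0.124 / 0.012 | not run |
| 95% / 85% | above 10 points | about 0.08 / 0.03 | about 0.05 |
| 97% / 77% | above 10 points | about 0.11 / 0.02 | about 0.05 |

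Across the scenarios run, the stratified test stayed between about 0.05 and 0.056.

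**6. Cost in power.** Over all allocations the stratified test has equal power or about 1 point more. The gain appears when the centres differ by 20 points; there is no loss when they do not differ.

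**7. If the list is already stratified by centre.** The plain test then becomes slightly conservative: type I error is 0.046 with rates of 95%/85% and 0.043 with 97%/77%. The analysis should reflect the strata in that case too.

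**The case against.** The strongest reply is that chance imbalance is what a randomisation-based test already allows for. That stands: error is nominal when averaged over allocations (step 4). Stratifying the allocation alone changes little, with power of 0.674 without strata and 0.670 with balance at 95%/85%. A 1.5-point shift is also modest beside sampling error. At about 94% success and 85 per arm the standard error is √(2 × 0.94 × 0.06/85) = 3.6 points, so the shift is about 0.4 standard errors. What remains is the conditional argument: once the imbalance is known, the nominal rate no longer describes the trial in hand, and a stratified estimate restores it.

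A reader might infer that allocation is unstratified. The document does not support that. It is a condensed article, the allocation sentence is silent on strata, and REDCap can hold a stratified list. Silence of this kind is not a fault.

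A reader might also infer from "PS = 6cmH_2_O for tubes > 5mm, 8cmH_2_O for tubes 4 - 5mm, and 10cmH_2_O for tubes ≤ 3.5mm" that three different treatments are wrongly pooled. The SBT Groups section defines one regimen adjusted to tube size, and the Introduction gives tube resistance as the argument for pressure support. Pooling is the intended comparison, and the ratio of set pressures does not measure how far the treatment contrast varies.

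Finally, the article reports no reintubation rates by centre and does not describe different extubation practice. The worksheets are common to both units. The size of any centre effect is therefore assumed.

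**Conclusion.** The point holds as an improvement to the stated analysis. The named test takes no account of centre in a trial of two unlike units, although centre is known for every child. The result would not be invalid or biased, and the documents do not support saying so. The gain is an error rate that stays near 0.05 whatever centre imbalance occurs, instead of about 0.08 or 0.03 (centres 10 points apart) or about 0.11 or 0.02 (20 points apart) when imbalance exceeds 10 points.

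These figures assume 170 children, an equal split between centres, allocation without centre strata, and a CPAP deficit of 10 points in both centres. If the centres have the same success rate, the two analyses perform alike.

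**What to change.** In Statistical methods, name as the primary analysis a centre-stratified risk difference (CPAP minus PS) with Mantel-Haenszel weights and Farrington-Manning or Miettinen-Nurminen variance, judged by the 90% confidence interval against the same 10-point margin. Keep the unstratified Farrington-Manning test as a sensitivity analysis. Add one sentence saying whether the allocation list is stratified by centre; the list itself need not change.

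The cost is two or three sentences and a few lines of analysis code. There is no added recruitment and no loss of power in the scenarios checked. Because the trial is open-label, the change should be dated and made before anyone examines outcomes by arm.

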### SBT Groups

–**CPAP Group:** SBT for 1 hour with positive end-expiratory pressure (PEEP) and no PS. The PEEP and FiO_2_ will remain the same as during the ERT.–**PS Group:** SBT for 1 hour with PEEP and PS, adjusted by tracheal tube size: PS = 6cmH_2_O for tubes > 5mm, 8cmH_2_O for tubes 4 - 5mm, and 10cmH_2_O for tubes ≤ 3.5mm.

### Primary outcome

Successful liberation from invasive MV is defined as no need for reintubation within 48 hours post-extubation.

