### Secondary outcomes

–First SBT pass rate–Need for post-extubation respiratory support (high-flow nasal cannula or noninvasive ventilation)–Length of pediatric ICU stay

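### The primary outcome is counted from extubation although randomisation precedes the breathing trial, so it has no valid value for randomised children who are not extubated

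*Protocol article*

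**What the plan says.** Order of events (Interventions): "After passing the ERT, which is shown in table 1, patients will be randomized to either the PS or CPAP group". The one-hour SBT by the allocated method follows randomisation.

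Route to extubation (Interventions, note to Table 2): "If all the above checks in table 2 are NO at the end of a 1-hour spontaneous breathing test, inform the pediatric intensive care unit". Those informed then arrange the extubation. The same note foresees that a child who passes may still stay intubated: "If, for some reason, the patient is not extubated, justify". The text shown gives no route for a child who fails.

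Primary outcome: "Successful liberation from invasive MV is defined as no need for reintubation within 48 hours post-extubation". The abstract starts the clock at the same point: "The primary outcome is successful liberation from invasive mechanical ventilation for at least 48 hours post-extubation". So does the Discussion.

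Analysis (Statistical methods): "The primary analysis will be performed according to the intention-to-treat principle". Non-inferiority is judged by the Farrington-Manning test, "with a 90% confidence interval to confirm the non-inferiority of CPAP compared to PS". The margin is 10% (Sample size and power calculation).

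The SBT result enters the outcomes only as a secondary one: "First SBT pass rate".

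**The concern.** Three stated rules do not fit together. Randomisation comes before the SBT. The SBT, which is the randomised intervention, governs who reaches extubation. The primary outcome is measured only from extubation. Intention-to-treat requires a value for every randomised child, and the definition gives none to a child who was not extubated.

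Applied only where it has meaning, the outcome compares children selected after randomisation by a step that differs between the arms. Applied word for word, it makes a child who stayed on the ventilator a success, because that child was not reintubated.

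The Introduction reports that pressure support may give more false-positive readiness, so the article itself treats it as the easier test to pass. A plausible cost of testing without it is that some children who are ready fail and stay ventilated longer. An outcome that starts at extubation does not register that cost. The trial is open-label, so a classification chosen late could be chosen with knowledge of the allocations.

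**Working it through.** **Inputs.** From the article: 10-point margin; 90% confidence interval, which is one-sided 5% for non-inferiority; 170 recruited, so 85 per arm. Assumed, because the article gives no such rates: SBT pass s = 0.90 with pressure support and 0.80 with CPAP; q = 0.94 free of reintubation once extubated, in both arms.

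**The plan's own figure.** The article states 94 per group but no success rate, so the figure can only be solved backwards. With n = (1.645 + 1.282)² × 2p(1 − p) / 0.10², p = 0.942 gives 8.564 × 0.1093 / 0.01 = 93.6, so 94. With the Farrington-Manning variance the rate lies between 95.3% (99 per arm) and 96% (90 per arm). Rates this high would suit a rate among extubated children, but the article does not confirm that. They are why q = 0.94 is used here.

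**Three classifications, no later extubation.** The approximate probability of declaring non-inferiority is Φ[(0.10 + D)/SE − 1.645], where D is CPAP minus pressure support.

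| Classification | Success, PS | Success, CPAP | D (points) | SE | Formula | Simulated |
|---|---|---|---|---|---|---|
| Extubated only: q | 94.0% | 94.0% | 0 | 0.0396 | 0.81 | 0.81 |
| Never extubated = success: 1 − s + sq | 94.6% | 95.2% | +0.6 | 0.0337 | 0.93 | 0.92 |
| All randomised, not extubated = not a success: sq | 84.6% | 75.2% | −9.4 | 0.0610 | 0.06 | 0.06 |

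The first row has 0.90 × 85 = 76.5 and 0.80 × 85 = 68 children. The simulation uses a Wald 90% interval. With the Farrington-Manning test that the article names, the three simulated figures are 0.74, 0.88 and 0.06, so the contrast remains.

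**Later extubation.** Suppose half of those who fail the first SBT are extubated later and counted. The proportions extubated become 0.95 and 0.90, and success among all randomised is 0.95 × 0.94 = 89.3% and 0.90 × 0.94 = 84.6%, so D = −4.7 points. With SE = 0.0515 the formula gives 0.27; simulation gives 0.28 (0.26 with Farrington-Manning). Extubated-only analysis of the same trials gives about 0.84.

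**Equal pass rates.** With 90% in both arms, success is 94.0%, 94.6% or 84.6% in both arms under the three classifications, so D = 0 each time. There is no bias, although the power still depends on the classification.

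**A more extreme case.** With pass rates of 85% and 70% and no later extubation, the all-randomised rates are 79.9% and 65.8%, D = −14.1 points, outside the margin. The three probabilities are 0.77, 0.95 and 0.013. If half of the failures are later extubated, the rates are 87.0% and 79.9% (D = −7.1 points) and the all-randomised probability is about 0.13.

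**Power for an all-randomised outcome.** At 80% success in both arms and 85 per arm, SE = √(2 × 0.80 × 0.20/85) = 0.0614 and power = Φ(0.10/0.0614 − 1.645) = 0.49. At 84.6% in both arms, 90% power needs 8.564 × 2 × 0.846 × 0.154 / 0.01 = 223.1, so 224 per arm (229 with the Farrington-Manning variance).

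**The case against.** **The article does not say that these children are dropped or counted as successes.** This stands. The label speaks of liberation from ventilation, so a child still intubated can fairly be read as not liberated and, under intention-to-treat, as not a success. A child who fails once may also be extubated later and assessed then; the word first in the secondary outcome points that way. A reader might infer that the plan as written favours CPAP. The text does not support that: it leaves the classification open, and any bias depends both on the choice made and on CPAP failing more children.

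**The size is assumed.** This also stands. The article gives no SBT failure, later extubation or reintubation rate. The −14.1 points are an extreme case. Even the −9.4 points lie just inside the margin, so a declaration there is not strictly a false one. With 6% reintubation in both arms, the extubated-only analysis hides a difference; it does not make CPAP look better.

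**The 20% attrition shows that non-extubated children will be dropped.** A reader might infer this, since the outcome is short-term. The article gives no reason for the 20%, and that sentence has its own arithmetic problem (188 needed, 170 recruited). It is not evidence of such a plan.

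**A later test by the other method could produce a CPAP success.** The text shown does not settle this, but Figure 1 is not shown and the full protocol may cover it. It is not part of this point.

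**The harm is visible elsewhere, and reintubation suits the aim.** First SBT pass rate and length of stay are secondary outcomes, and reintubation is a sensible measure of false-positive readiness. That is a case for keeping it as a labelled conditional outcome. It does not give the primary outcome a value for every randomised child.

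**Conclusion.** The point holds as a defect in a stated rule, not as a detail left to an analysis plan. The primary outcome has no valid value for randomised children who fail the SBT or are not extubated, and this conflicts with the intention-to-treat analysis.

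The consequence is conditional. Leaving these children out, or counting them as successes, biases towards non-inferiority of CPAP if CPAP fails more children than pressure support. With equal failure rates no classification shifts the comparison. Under the assumed 90% and 80% pass rates, the choice of classification moves the chance of declaring non-inferiority between about 6% and 92%. Later extubation narrows the gap but does not close it: 28% against 84% when half of the failures are later extubated.

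The classification can therefore decide the trial's result, and it should be fixed before any outcome data are seen.

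**What to change.** Define the primary outcome for all randomised children: extubated within a fixed window from randomisation, its length chosen by the investigators, and free of reintubation for 48 hours after that extubation. Any other randomised child is not a success. Use the same wording in the abstract, the Primary outcome section, the Discussion and the registry entry. Keep reintubation among extubated children as a secondary outcome, labelled as conditional on extubation. How repeat SBTs are done is for the investigators to state.

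Restate the sample size at the expected all-randomised success rate, and give that rate.

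Cost: the rewording needs no new data. The success rate will be lower, so power falls to about 50% with 85 per arm at 80% success in both arms, one-sided 5%. At 84.6% success, 90% power needs about 224 per arm against the stated 94. The loss is smaller if later extubations within the window count, because the success rate is then higher. If a larger sample is not feasible, the lower power should be stated openly.

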## DISCUSSION

We present the design and rationale of the "Non-inferiority randomized controlled trial of SBT in children with and without pressure support", which aims to determine whether CPAP alone during an SBT is non-inferior to CPAP combined with PS in predicting successful extubation in mechanically ventilated children. The trial is designed as a multicenter, randomized, non-inferiority study, with the primary outcome being successful liberation from MV for at least 48 hours post-extubation. Secondary outcomes include the need for additional respiratory support post-extubation and the length of pediatric ICU stay. Protocol publication increases research transparency, facilitates future publication of results, avoids research duplication, and informs the community.

There is a scarcity of clinical trials in patients under MV, particularly on the best practices related to weaning and liberation from MV. This study will provide valuable data to guide clinical decision-making and influence future guidelines on weaning from MV in pediatric critical care.

A limitation of this trial is that the unblinded design may introduce bias. The 1-hour SBT duration is based on current practice, but this study may not address the optimal duration.

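### The primary outcome carries no survival condition, so a child who dies without a tube within 48 hours of extubation can be scored as successfully liberated

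*Protocol article*

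**What the plan says.** The Primary outcome section of the Protocol article consists of one sentence, in which successful liberation is "defined as no need for reintubation within 48 hours post-extubation".

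The outcome is worded twice more. The abstract (Methods) has "successful liberation from invasive mechanical ventilation for at least 48 hours post-extubation", and the Discussion has "successful liberation from MV for at least 48 hours post-extubation". Neither mentions death.

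Three other places bear on the point:

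- Exclusion criteria lists "Palliative care patients". This is applied at entry.
- Statistical methods states: "The primary analysis will be performed according to the intention-to-treat principle". The same section assesses non-inferiority with the Farrington-Manning test, "with a 90% confidence interval to confirm the non-inferiority of CPAP compared to PS".
- Secondary outcomes lists the first SBT pass rate, respiratory support after extubation and length of PICU stay. Mortality is not listed. Deaths would be captured only through the reporting described under Harms and adverse events, which is not tied to the primary outcome.

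**The concern.** A definition built only on reintubation leaves two groups of extubated children without a clear place: those who die in the 48 hours without being reintubated, and those for whom a decision is made after extubation not to reintubate. On the literal wording, a child in either group can be scored as a success. Because the analysis is by intention to treat, these children stay in the denominator and must receive a value.

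Excluding palliative care patients at entry does not settle this, since the decisions at issue arise after randomisation. One of the two units, "which has a 19-bed pediatric ICU and is an oncologic center", is a setting where they could plausibly occur.

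The trial seeks to show that CPAP is not worse than PS. If untubed deaths were more frequent after CPAP, the definition would credit them to CPAP as successes and push the result towards the conclusion the trial hopes to reach.

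**Working it through.** **Step 1: does any section supply a survival condition?**

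| Section | Content on this point | Requires survival? |
|---|---|---|
| Primary outcome | no need for a new tube in 48 hours | No |
| Abstract (Methods), Discussion | liberation lasting at least 48 hours | Not stated |
| Exclusion criteria | palliative care, at entry | Does not reach events after randomisation |
| Secondary outcomes | three outcomes, none of them mortality | No |
| Statistical methods | analysis by intention to treat | No scoring rule for death |

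The wording in the abstract and the Discussion could suggest that a child who dies at, say, hour 12 was not liberated for 48 hours. But the Primary outcome section is where successful liberation is formally defined, and it defines it by the need for reintubation alone.

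**Step 2: how much does one child move the result?**

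Inputs from Sample size and power calculation: 94 per group, a recruitment target of 170, 20% attrition, and a 10% margin, read here as 10 percentage points. Equal allocation is assumed. The size per arm is then:

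- 94, as calculated in the article
- 170 / 2 = 85, if the target is met without losses
- 170 × 0.8 / 2 = 68, if 20% are lost

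The shift per misclassified child is 1/n:

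| n per arm | Shift in that arm's success rate | Children equal to the 10-point margin (0.10 × n) |
|---|---|---|
| 94 | 1/94 = 1.06 points | 9.4 |
| 85 | 1/85 = 1.18 points | 8.5 |
| 68 | 1/68 = 1.47 points | 6.8 |

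**Step 3: in which direction?**

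Let D_C and D_P be the untubed deaths scored as successes in the CPAP and PS arms. The observed difference in success (CPAP minus PS) then exceeds the difference with deaths counted as failures by (D_C − D_P)/n. An excess in CPAP helps the non-inferiority claim, an excess in PS hinders it, and equal numbers cancel in the difference. Nothing in the article indicates which to expect.

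**Step 4: how many failures are there to compare with?**

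The article states neither the assumed success rate nor alpha, so its 94 per group can only be solved backwards, not reproduced. The unpooled formula with zero true difference is n = 2p(1 − p)(z_α + z_β)² / 0.10². With n = 94 and 90% power it gives:

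- one-sided alpha 0.025: p = 0.953, failure 4.7%
- one-sided alpha 0.05 (what a 90% interval implies): p = 0.942, failure 5.8%
- one-sided alpha 0.10: p = 0.922, failure 7.8%

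A Farrington-Manning calculation at one-sided 0.05 needs 103 per group even at 95% success, so on that basis 94 would imply a failure rate below 5%. Taking 5.8% as an illustration, expected failures are 0.058 × 68 = 3.9 to 0.058 × 94 = 5.5 per arm. On the stated assumptions failures are few, so single children matter. Steps 1 to 3 do not depend on this back-calculation.

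**The case against.** The strongest reply is that the definition speaks of *need* for reintubation and not of reintubation itself. A child dying of respiratory failure, or one for whom an indicated tube is withheld, can be said to have needed it and so to have failed. Together with the 48-hour wording in the abstract and the Discussion, this makes the article open to two readings. That much stands: a reader might infer that the plan positively scores every untubed death as a success, and the text does not go so far. What does not follow is that the problem disappears. The favourable reading depends on an unwritten, case-by-case judgement of need, in a trial whose Discussion concedes that lack of blinding may introduce bias. It also fits poorly with a sudden death from a non-respiratory cause.

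A second reply is that a condensed article leaves the handling of death to a full protocol or analysis plan. That would excuse silence on analysis detail. Here the article states the endpoint definition itself, and a later document that scored death as failure would be changing or qualifying that definition.

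A third reply is that such events will be rare: children are randomised after passing a readiness test, they are considered for extubation after a clean one-hour breathing trial, and palliative patients are excluded. This is fair. A reader might infer from the oncology unit that these deaths will be common, but the nature of a unit is not an event rate and the article gives none.

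**Conclusion.** The point holds as a flaw in a stated definition. As written, an untubed death within 48 hours can be scored as success, and nothing elsewhere in the article prevents it.

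The size is known only per child: about 1.1 to 1.5 percentage points in the affected arm, or 11% to 15% of the margin, assuming equal allocation and 94 down to 68 children per arm. The total effect cannot be computed without a death rate and is probably small.

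A reader might infer that the flaw biases the trial towards CPAP, or equally conceals a deficit in either arm. The article supports neither. The test runs in one direction, only an excess of such deaths in the CPAP arm favours a false non-inferiority claim, and there is no evidence that an imbalance is expected.

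The correction is worth making because it is cheap and concerns the primary outcome, not because a large distortion has been shown.

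**What to change.** Define the primary outcome as alive and not reintubated at 48 hours after extubation, so that death within 48 hours counts as failure. Use the same wording in the abstract, the Primary outcome section and the Discussion, and in the registry entry if it differs. Report deaths and reintubations within 48 hours separately by arm.

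For children with a documented decision after extubation not to reintubate, fix the scoring rule in advance, for example failure in a sensitivity analysis. Do not rest it on staff judging, child by child, whether reintubation would otherwise have happened. That is a counterfactual judgement made by people who know the allocation, and it would bring back the subjectivity that the change is meant to remove.

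The cost is a short amendment, best made before outcome data are seen, one more item to record (vital status at 48 hours), and a slightly lower success rate. The decision not to reintubate also has to be documented so that the rule can be applied.
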